## Sample size and patient population

Patients undergoing VA-ECMO (regardless of the indication for the therapy) will be enrolled. The initial plan is to enroll patients within 1 year, with no loss to follow-up. Based on a previous VA-ECMO study investigating echocardiographic predictors of outcome (18), we estimated a 92.2% statistical power to detect a 20% effect with respect to the primary composite outcome, by assuming an 30% weaning failure rate in a sample size of 100 patients. Importantly, the feasibility of speckle-tracking analysis with transoesophageal echocardiography (TOE) was previously reported to be 90% (19). Therefore, we aim to enroll 110 subjects, a sample size which exceeds previous cardiac imaging studies of the field able to demonstrate association of echocardiography measures with outcome (18, 20). Both peripherally and centrally cannulated subjects are candidates for participation. Considering that the two populations are typically quite different in terms of indication for the therapy (ACS- or decompensated chronic heart failure-associated CS vs. cardiac surgery population), a balanced enrollment of the two methods will be facilitated by interim assessment at 50% of the enrollment. All LV venting options are eligible for enrollment, however, if utilized, the mode of LV unloading (central left atrial vent, Impella, transaortic LV pigtail catheter etc.) will also be collected. Notably, LV unloading significantly influences ventricular mechanics (21). Still, due to the highly variable institutional practices in terms of LV unloading, the study protocol does not exclude certain techniques.

The study aims to include a broad spectrum of patients; therefore, the exclusion criteria are mainly technical contraindications of the measurements. Patients 18 years or older on VA-ECMO will be enrolled, if TOE is feasible or the transthoracic echo window also enable sufficient image quality for further analysis. The inclusion and exclusion criteria are listed in Table 1.

**Table 1 T1:** Inclusion and exclusion criteria of the study.

Inclusion criteria	Exclusion criteria
Patients 18 years old or older	Younger than 18 years old
Cardiogenic shock refractory to conventional therapy, requiring VA-ECMO implantation	Written informed consent cannot be collected

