### Echocardiographic examination

Echocardiographic acquisitions must be performed between 48 and 72 h following the initiation of MCS. Inotropic and vasopressor support at the time of the examination are based on the clinician's discretion. In order to ensure consistently high image quality, TOE is strongly recommended, however, in patients with good transthoracic echocardiographic window and with relevant concerns regarding TOE (e.g., awake and extubated, clinically relevant oropharyngeal bleeding), transthoracic approach is also acceptable. ECG-gated images and loops will be obtained and at least 3 cardiac cycles will be recorded. The detailed TOE acquisition protocol is depicted in Supplementary Data S1.

3D echocardiographic loops are not mandatory parts of the protocol, however, the acquisition of such datasets are strongly encouraged.

Two sets of acquisitions will be obtained: the first set will be performed with the current MCS minute volume. The second set will be recorded after setting a predefined minute support normalized to the body surface area of the patient (1.1 L/m^2^/min). After changing to the predefined MCS minute volume, only a short (1 min) waiting period is recommended, as the common clinical experience is that biventricular load rapidly changes along with the altered MCS settings.

In order to calculate non-invasive myocardial work indices, systolic and diastolic blood pressure will be recorded at the beginning of both acquisition sets. If the LV does not eject at the time of echocardiographic examination, mean arterial pressure will be used.

Echocardiographic measurements will be performed offline in an Echocardiography Core Laboratory (Semmelweis University, Heart and Vascular Center, Budapest, Hungary) by an experienced operator, blinded to the clinical data and outcome of the patients. All participating sonographers of the Centers will be certified by the Echocardiography Core Laboratory according to the international standards (22).

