Cardiac chamber quantification will be based on the most recent guidelines. LV volumes and ejection fraction (EF) will be calculated using the biplane Simpson method. LV longitudinal strain will be measured using dedicated software (TomTec 2D AutoStrain, TomTec Imaging Systems, Unterschleissheim, Germany). LV non-invasive myocardial work indices will be calculated using the exported longitudinal strain data of TomTec and a custom-made software. The principles of myocardial work estimation will correspond with the calculation method of Russell et al. (23).

First, the opening and closure timepoints of the aortic and mitral valves are identified on the echocardiographic loops by visual assessment on a medoesophageal long-axis view. Next, using these temporal reference points, both curves are dissected into four sections (isovolumetric contraction, ejection, isovolumetric relaxation, and diastolic filling), with each section of the strain curve being matched with the corresponding section of the simulated pressure tracing. Due to the different temporal resolution of the datasets, the timestamps of the pressure and strain tracings are normalized in each section. The strain values are interpolated for the timestamps based on the LV pressure recording. The four sections of the recordings are subsequently concatenated, and pressure-strain loops are plotted. The instantaneous power is calculated by multiplying the strain rate (obtained by differentiating the strain curve) and the instantaneous LV pressure.

Global myocardial work index (GWI) is computed by integrating the power from mitral valve closure until mitral valve opening. Work performed during myocardial stretching means energy loss and was defined as negative work in contrast to positive work performed during myocardial shortening. Global constructive work index (GCW) is the sum of global positive work, while global wasted work (GWW) is the sum of negative global work. As a measure of global myocardial efficiency, global work efficiency (GWE) is also calculated as the ratio of the wasted work to the constructive work.

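### For a non-ejecting ventricle the plan inserts mean arterial pressure, which is an upper bound on LV pressure, and its curve matching relies on aortic valve events that do not occur

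*Protocol article*

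**What the plan says.** Under Echocardiographic examination, the pressure input for the work indices is normally the arterial reading: "systolic and diastolic blood pressure will be recorded at the beginning of both acquisition sets". The exception is: "If the LV does not eject at the time of echocardiographic examination, mean arterial pressure will be used".

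The same section then describes one algorithm for all patients. Valve events come first: "the opening and closure timepoints of the aortic and mitral valves are identified on the echocardiographic loops by visual assessment". Strain and simulated pressure are next cut into sections and matched piece by piece: "both curves are dissected into four sections (isovolumetric contraction, ejection, isovolumetric relaxation, and diastolic filling"). Power follows: "The instantaneous power is calculated by multiplying the strain rate (obtained by differentiating the strain curve) and the instantaneous LV pressure". Finally: "Global myocardial work index (GWI) is computed by integrating the power from mitral valve closure until mitral valve opening".

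Non-ejecting patients are not excluded, and the section on sample size and population says: "All LV venting options are eligible for enrollment". Under Assessment of endpoints, the main objective is to show whether work indices predict outcome better than EF, GLS or LV outflow tract VTI. The Statistical analysis section describes no separate handling of non-ejecting patients.

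**The concern.** There are two difficulties.

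- **The pressure.** In an ejecting ventricle the arterial systolic pressure reflects what the ventricle generates. In a non-ejecting one the arterial pressure is sustained by circuit flow and vascular tone. One variable name then carries inputs with two meanings, and the error goes one way.
- **The timing.** The matching step uses aortic valve events that a closed valve does not produce.

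At stake is the comparison of the work indices with EF, GLS and VTI through logistic models, AIC, ROC curves and Youden cutoffs. Only the work indices carry this error. The article's case for them is that they handle altered load better, yet in these patients the index takes in the pressure that the ventricle fails to overcome. The two acquisition sets are taken at different circuit flows, so a patient may eject in one set and not in the other. The pressure input would then change type within that patient.

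**Working it through.** The documents state no figure on this point, so there is none to reproduce.

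**1. What MAP represents here.** A closed aortic valve means LV pressure stays below aortic pressure. With little pulsatility, aortic pressure is about MAP. Hence peak LV pressure is at most about MAP.

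**2. Effect on the indices.** From the article: power = strain rate × LV pressure, integrated from mitral closure to mitral opening. Write LV pressure as P_max × f(t), where f is a fixed shape with peak 1 and zero baseline. Then

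GWI = P_max × ∫ f(t) × shortening rate dt.

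The integral does not depend on P_max, so computed work / true work = MAP / true peak. The same holds for GCW and GWW. The article does not say how a single mean value scales the simulated curve; I assume that it replaces the peak.

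With assumed MAP 65 mmHg:
- true peak 55 mmHg: 65/55 = 1.18
- true peak 30 mmHg: 65/30 = 2.17

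A numerical integration with a half-sine pressure curve, assumed MAP 70 mmHg and several assumed strain curves gave:

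| Assumed true peak (mmHg) | Zero baseline: 70/peak | GWI factor with end-diastolic pressure 10 mmHg |
|---|---|---|
| 60 | 1.17 | 1.16–1.18 |
| 50 | 1.40 | 1.40–1.45 |
| 40 | 1.75 | 1.74–1.87 |
| 30 | 2.33 | 2.31–2.63 |

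*Sign.* The overstatement is of magnitude. With a wall that stretches on balance (end-diastolic pressure 10, true peak 40), GWI moved from −33.2 to −58.9.

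*GWE.* With zero baseline the pressure cancels from the ratio of wasted to constructive work. With end-diastolic pressure 10 the ratio changed by at most about 15% (2.738 to 3.141), far less than the work indices did.

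**3. Absolute size.** As a rough product of strain and pressure, all values assumed:
- Non-ejecting, strain 3%: 3 × 65 = 195 mmHg%, against 3 × 30 = 90 to 3 × 55 = 165. The excess is 30 to 105.
- Poorly ejecting, strain 5–6% at 80–90 mmHg: 5 × 80 = 400 to 6 × 90 = 540.

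The overstated value still ranks below the ejecting one. It would reach 400 only at a strain of 400/65 = 6.2%. At 8% it would be 8 × 65 = 520, against 8 × 30 = 240 to 8 × 55 = 440, and ranks could change.

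**4. Segmentation.** The sections and their bounding events are:
- isovolumetric contraction: mitral closure to aortic opening
- ejection: aortic opening to aortic closure
- isovolumetric relaxation: aortic closure to mitral opening
- filling: mitral opening to mitral closure

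With the aortic valve shut, two of the four boundaries are missing, and three of the four sections cannot be delimited as printed. The GWI window survives because it runs between mitral events only.

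**The case against.** The strongest reply has four parts.

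- **Timing.** The authors foresaw non-ejection and set a pressure for it. GWI needs only mitral events, and a timing fallback may sit in the custom software, the supplements or the full protocol, none of which is shown. This stands. A reader might infer that the calculation is impossible in these patients. The text supports less: the printed steps do not fit together and need reconciling.
- **Who is affected.** A reader might infer that work is inflated in the sickest patients. The Discussion does not support this. It says that raised afterload can impair ejection while contractile strength is preserved, so a closed valve need not mean the worst ventricle. With net stretch, GWI also moves down, not up.
- **Effect on the analysis.** Strain is probably small in a non-ejecting ventricle, so a large ratio may be a small absolute shift, and ROC and Youden analyses depend on rank. This stands as a limit on the harm. It depends on assumed strains, and a vent gives blood another way out of the heart, so appreciable shortening with a closed valve cannot be ruled out.
- **Direction.** If non-ejecting patients do fare worst, raising their work values weakens the index and works against the study's hypothesis. This is fair: the documents do not fix the direction of bias in the association.

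None of this makes MAP an estimate of LV pressure.

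**Conclusion.** The concern holds in a limited form. The stated rule puts an upper bound on pressure where an estimate is needed, so the magnitudes of GWI, GCW and GWW are overstated in non-ejecting ventricles. GWE is little affected, and EF, GLS and VTI do not use the substituted pressure. The factor is about 1.2 to 2.2 if MAP is 65 mmHg and true peak LV pressure 30 to 55 mmHg. Both pressures are assumptions, as is the use of MAP as the peak of the curve. The documents do not give the number of such patients, and they do not show that any patient would change rank or cross a cutoff. The passage on MAP and the passage on section matching must be reconciled.

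**What to change.** - Record ejection status (aortic valve opening or not) at each of the two acquisition sets. The core laboratory can read it from images already planned.
- Do not treat MAP-based work values as equivalent to values from ejecting ventricles. Add a non-ejecting indicator to the models. Put it in the comparator models too, so that AIC does not credit the work index with ejection status.
- Repeat the main comparison with EF, GLS and VTI in ejecting ventricles only, using the same patients for every measure. This also covers the single-marker ROC and Youden analyses, where an indicator cannot enter.
- State the segmentation used when the aortic valve stays closed, and how MAP scales the simulated pressure curve.

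Assigning non-ejecting patients the worst rank on work is not advisable. It assumes that lost ejection means lost contractility, against the Discussion, and it would build VTI information into the index that is being tested against VTI.

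Cost: one flag per acquisition set, one extra model term, slightly fewer patients in the sensitivity analysis, and a few sentences of text. No image acquisition or patient care changes.

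### Work is scored as constructive or wasted by shortening versus stretching alone, with no exception for isovolumetric relaxation, so GCW, GWW and GWE can misorder ventricles

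*Protocol article*

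**What the plan says.** All the relevant text is in the Protocol article under Echocardiographic examination.

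- **Phases.** Using the visually marked valve times, "both curves are dissected into four sections (isovolumetric contraction, ejection, isovolumetric relaxation, and diastolic filling". Isovolumetric relaxation is thus identified separately, but the phases serve only to align the strain curve with the simulated pressure curve.
- **Power.** "The instantaneous power is calculated by multiplying the strain rate (obtained by differentiating the strain curve) and the instantaneous LV pressure".
- **Interval.** "Global myocardial work index (GWI) is computed by integrating the power from mitral valve closure until mitral valve opening". This covers isovolumetric contraction, ejection and isovolumetric relaxation.
- **Sign rule.** "Work performed during myocardial stretching means energy loss and was defined as negative work in contrast to positive work performed during myocardial shortening". No phase is named.
- **Indices.** "Global constructive work index (GCW) is the sum of global positive work, while global wasted work (GWW) is the sum of negative global work", and "global work efficiency (GWE) is also calculated as the ratio of the wasted work to the constructive work".
- **Source.** "The principles of myocardial work estimation will correspond with the calculation method of" a cited publication that is not among the documents. The calculation itself runs in custom-made software.
- **Non-ejecting ventricles.** "If the LV does not eject at the time of echocardiographic examination, mean arterial pressure will be used".

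**The concern.** What a change in length means depends on the phase. Before aortic closure, shortening contributes to ejection and stretching works against it. After aortic closure, lengthening is the relaxation that a working ventricle has to perform, and shortening can no longer eject blood. A rule that looks only at the direction of deformation files normal relaxation under waste and post-systolic shortening under constructive work.

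The main objective (Assessment of endpoints) is whether the myocardial work indices, in the plural, are better prognostic markers than conventional measures. The Statistical analysis section takes parameters through regression, AIC comparison and ROC curves, then dichotomizes at the Youden cutoff. A misordering in GCW, GWW or GWE would pass into each of these steps. All left ventricular venting modes are eligible, and the Discussion says that one of them shortens the isovolumetric phases. The misassigned component may therefore also vary with the unloading device.

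**Working it through.** The plan gives no figure to reproduce here, and no strain or pressure values. The check is a sign argument, followed by an illustration on assumed curves.

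**Sign argument (from the article alone).** Taking shortening as positive, work over a small step is −(change in strain) × pressure. Left ventricular pressure is above zero throughout the interval, so the sign of the work follows the strain rate only. Any lengthening between aortic closure and mitral opening therefore enters GWW, and any shortening there enters GCW. GWI is the net integral and does not depend on how the parts are labelled.

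**Illustration, curve 1 (all values assumed).** Pressure runs in straight lines through 8 mmHg at mitral closure (0 ms), 67.5 at aortic opening (60 ms), 90 at 200 ms, 72 at aortic closure (340 ms) and 8 at mitral opening (430 ms). Strain shortens by 8 points, evenly, between 60 and 340 ms.

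- Mean pressure during ejection: [(67.5 + 90)/2 + (90 + 72)/2]/2 = (78.75 + 81)/2 = 79.875 mmHg. Ejection work: 8 × 79.875 = 639.0 mmHg%.
- Pressure at 370 ms: 72 − 64 × 30/90 = 50.67 mmHg.
- Lengthening placed at 370 to 430 ms: mean pressure (50.67 + 8)/2 = 29.33, so 29.3 mmHg% per point.
- Post-systolic shortening placed at 340 to 370 ms: mean pressure (72 + 50.67)/2 = 61.33, so 61.3 mmHg% per point.

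GWE is taken as the article writes it, GWW/GCW. By phase means that the roles of shortening and lengthening are swapped after aortic closure.

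| Loop | GWI | GCW / GWW / GWE as written | GCW / GWW / GWE by phase |
|---|---|---|---|
| 1 point of lengthening in relaxation | 639.0 − 29.3 = 609.7 | 639.0 / 29.3 / 0.046 | 668.3 / 0 / 0 |
| 1 point of shortening after aortic closure | 639.0 + 61.3 = 700.3 | 700.3 / 0 / 0 | 639.0 / 61.3 / 0.096 |

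The two loops change places. As written, the relaxing ventricle has the more wasted work (29.3 against 0); by phase it has the less (0 against 61.3). Lengthening of 0.5 to 2 points gives an as-written GWW of 14.7 to 58.7, where the phase-specific value is 0.

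With 4 points of ejection shortening the ejection work is 319.5, and the GWE contrasts double: 29.3/319.5 = 0.092 against 0 for the first loop, and 0 against 61.3/319.5 = 0.192 for the second.

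**Illustration, curve 2 (also assumed).** Smooth curves with pressure 90/60 mmHg, 10 mmHg at mitral opening, 90 ms of isovolumetric relaxation and strain of about −10%. Lengthening of 1 to 2 points gives an as-written GWW of 29 to 61, against 0 by phase. With 1.5 points of post-systolic shortening, GWW is 0 as written against 66 by phase, and GCW is 757 against 691 (66/691 = about 10% higher).

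The range of roughly 60 to 66 mmHg% for post-systolic shortening thus joins 1 point on curve 1 with 1.5 points on curve 2. It shows an order of magnitude and is not a bound: 1.5 points on curve 1 would give 1.5 × 61.3 = 92.

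**The case against.** The strongest reply is that the article defines its own terms. Stretching is negative, shortening is positive, and the two sums follow; nothing in the document defines relaxation lengthening as constructive. The cited method may use this sign rule, or it may be phase-specific and only condensed here. A reader might infer that the article misstates its source. The documents do not support that, because the source is not shown and the article claims agreement only in principle. What remains is the consequence of the stated rule, which needs no outside source.

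The written rule also has two practical merits. It keeps GWI = GCW − GWW, which a phase-specific rule does not: in the second loop above, GWI is 700.3 while the phase-specific difference is 639.0 − 61.3 = 577.7, and net work then exceeds constructive work. It also needs no aortic closure time, which is not available when the ventricle does not eject, a case that the article foresees. Both points stand and are costs of the change.

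The size is also open to challenge, and rightly. The curves are assumed, the zero in the first loop arises because no systolic stretch was put in, and length change during isovolumetric relaxation may be small if a single global strain curve is used.

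Three stronger readings are tempting and go too far:

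- That the indices would be ranked backwards against outcome. The article contains no outcome data by index, so only misordering between kinds of loop can be shown.
- That normal diastolic filling also counts as waste. The interval sentence names only GWI, but the sentences that follow most naturally divide that same work.
- That the main objective is compromised as a whole. GWI, the work index used in the clinical examples under Assessment of endpoints, is untouched.

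**Conclusion.** The point holds as a weakness in a stated definition. Over an interval that includes isovolumetric relaxation, the rule necessarily counts lengthening after aortic closure as wasted and shortening there as constructive. GCW and GWW are affected directly, and GWE inherits the split whichever way up the ratio is written (the direction of that ratio is a separate matter). GWI is unaffected.

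That the labels are assigned this way follows from the article alone, given positive left ventricular pressure. That the assignment is undesirable rests on the physiology of the phase: relaxation requires lengthening, and a ventricle with a closed aortic valve ejects nothing. The size in this population is unknown. On the assumed curves it is tens of mmHg%, enough to reverse the order of two ventricles on GWW and GWE where little wasted work arises in systole.

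**What to change.** Before core-laboratory analysis:

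1. Make the assignment phase-specific with the valve times already marked. From mitral closure to aortic closure, shortening is constructive and lengthening wasted. From aortic closure to mitral opening, lengthening is constructive and shortening wasted.
2. State that GCW and GWW use the same interval as GWI.
3. Keep GWI as net work, and note that it will no longer equal GCW minus GWW.
4. For ventricles that do not eject, prespecify either how the end of systole is set or that GCW, GWW and GWE are not split by phase.
5. Report the sign-only version as a sensitivity analysis, which will also show how large the effect is in these patients.

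The cost is a small software change, a few sentences of definition and the loss of the simple GWI identity. No new data are needed, because the stored strain curves can be recomputed offline.
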